### Intervention

Participants randomized to IntACT will receive usual inpatient and outpatient services plus an interdisciplinary addiction care transition team consisting of a Board-certified addiction specialist, a nurse care manager, and a peer support specialist. The IntACT intervention provides: 1) in-hospital discharge planning support, 2) proactive post-discharge outreach and care coordination, 3) intensive care management and peer support, and 4) interim SUD and medical care coordination for up to four months post-randomization, with the goal of facilitating transition to longitudinal community-based care.

Upon randomization to the IntACT study arm, a member of the IntACT team (either peer navigator, clinician, or care manager) will deploy in person to the hospital to meet the participant, introduce their role, and exchange contact information. Initial contact will be made within 2 business days of randomization. The IntACT team member will discuss potential discharge needs with the participant and offer to facilitate any needed follow-up care at a partnering primary care/addiction medicine clinic or at a community site of the participant’s choosing. A one-page contact sheet will be provided to the patient with a IntACT team cell phone number and contact information for both our peer support specialist and care manager during the initial visit. If the patient leaves the hospital after randomization and before a member of the IntACT team can meet them, remote (e.g., telephone, text) outreach will be provided to complete the initial clinical meeting.

The IntACT team will continue to communicate with the patient and the care team ad hoc during the remainder of the hospitalization to address any care coordination needs that arise. At weekly IntACT clinical team meetings, the team will review the new participant’s hospital course, medications, and discharge needs. Ensuing discussion will focus on how best to leverage the interdisciplinary IntACT team to improve post-discharge care, including linkage to community supports, addressing biopsychosocial barriers to follow-up, and ensuring appropriate access to SUD and medical care.

Within two business days of discharge, the IntACT team will reach out to the patient, inquiring about symptoms and challenges faced after discharge, reviewing upcoming appointments and discharge medications, and assessing post-discharge substance use needs. If the team is unable to reach the participant, they will keep trying at least three times per week for the first three weeks after discharge. While follow-up visit frequency will be individualized, most people will follow up every 1–2 weeks via appointments at the partnering clinic or at another clinic/program of the participant’s choosing. Between-visit care through telephone and text outreach will be facilitated by IntACT team members. There are no additional clinical visits required of the patient to receive care through IntACT.

Participants randomized to Usual Care will receive standard services routinely available at the study site, including a hospital addiction consult service, discharge planning by hospital medical and social work teams, and referrals/follow-up options based on insurance and patient preference. Usual Care participants will not receive the structured IntACT components provided in the intervention arm. However, because IntACT team members work in clinical roles within the study site, participants in both arms may receive care that includes members of IntACT. If a Usual Care participant independently establishes care with the partnering primary care/addiction medicine clinic or other services (e.g., peer support) through standard referral pathways, this will be permitted and will be captured as part of outcome assessment.

After four months, the official intervention period will stop. Participants in both groups will still be able to continue care with their current medical and SUD treatment teams.

### Partnership of people with lived substance use experience in the intervention design

Individuals with lived substance use experience informed the design of the IntACT intervention both directly and indirectly. Prior to designing the intervention, we conducted qualitative interviews with people with lived SUD experience who had recently gone through a hospitalization about their care transition experiences [38]. Their expertise helped to formulate key elements of the intervention, including the outpatient-to-inpatient deployment of a primary care-based team. We also conducted a series of focus groups with both clinicians and people with lived substance use experience about key barriers and facilitators to SUD care transitions, components of an ideal care transition intervention, and priorities for future research [39]. Finally, the intervention team employs a peer support specialist, who provided direct formative feedback on IntACT’s approach, implementation, and evaluation during weekly pre-implementation meetings.

### Underlying conceptual framework for implementation

Two complementary conceptual frameworks will guide the implementation of the IntACT intervention: the Practical, Robust Implementation and Sustainability Model (PRISM) determinants framework and the Reach, Effectiveness, Adoption, Implementation, and Maintenance (RE-AIM) evaluation framework (Fig 2) [40,41]. RE-AIM specifically informs the evaluation plan for IntACT, including measures of reach, effectiveness, and implementation (e.g., feasibility). PRISM provides an overarching framework that accounts for the influence of real-world contextual factors such as clinician and staff attitudes and environmental/time constraints on intervention implementation.

**Fig 2 pone.0359281.g002:**
[figure not shown]
The PRISM and RE-AIM Implementation Frameworks adapted to the IntACT Study.

For the IntACT study, these complementary frameworks are integrated into an Implementation Research Logic Model (IRLM), [42] which is an organizational tool designed to synthesize implementation science frameworks into a single instrument that can be used to guide planning, execution, reporting, analysis, and reproducibility of implementation research (Fig 3). The IRLM has been used in multiple chronic disease implementation trials, highlighting its adaptability as an instrument [43–45]. In this study, the IRLM serves as a scaffold to integrate PRISM and RE-AIM for the planning, implementation, and evaluation of IntACT.

**Fig 3 pone.0359281.g003:**
[figure not shown]
Implementation Research Logic Model for the IntACT Intervention. Superscripted letters represent how implementation strategies are carried throughout the model to address specific barriers and inform mechanisms and outcomes design.

### Procedures and assessments

Key study-related procedures include participant enrollment and completion of iterative outcome assessments during and after the 4-month intervention period. These are outlined in Table 1.

**Table 1 pone.0359281.t001:** Assessment timeline for patient participants.

Study Procedure	Baseline	Month 2	Month 4	Month 6
Eligibility confirmation and consent	X			
Baseline survey (demographics and substance use history questionnaire)	X			
Study visit/ follow-up contact	X	X	X	X
SF-12	X	X	X	X
TAPS (Baseline only)	X			
PHQ-9	X	X	X	X
GAD-7	X	X	X	X
TLFB (Substance Use and ED/Hospital Encounters; Follow-up visits only)		X	X	X
Qualitative interview (n = 15; IntACT arm only)				X
Adverse event assessment		X	X	X

*Abbreviations: SF-12 = 12-Item Short Form Survey; TAPS = Tobacco, Alcohol, Prescription Medication, and Other Substances Tool; PHQ-9 = Patient Health Questionnaire-9; GAD-7 = Generalized Anxiety Disorder-7; TLFB = Timeline Follow-Back; IntACT = Interdisciplinary Addiction Care Transition team.*

If a potential participant meets eligibility criteria during the screening process, the research coordinator will explain the study objectives, procedures, and the randomized nature of the trial; assess interest in participation; and conduct a formal written informed consent process for those who wish to enroll. Once consented, participants will complete a baseline survey to finalize enrollment. Individuals unable to provide informed consent due to acute intoxication, withdrawal, medical illness, or psychiatric symptoms causing decisional impairment will not be enrolled. Trained research staff will re-approach these patients a minimum of 4 hours later to reassess their ability to consent to study participation. This assessment will be based on gestalt of the patient’s clinical status (e.g., intubation, sedation) and ability to answer questions in a linear and comprehensible manner. Once a participant is enrolled in the study, they will be randomized to receive the intervention or Usual Care.

For the clinician cohort, potentially eligible clinicians (i.e., those identified as providing clinical care to intervention patients) will be contacted by study staff either verbally or via secure institutional email and screened for eligibility based on inclusion/exclusion criteria. If eligible, research staff will assess interest in participation and conduct a formal informed consent process for those who wish to enroll. To minimize any possibility of undue influence, clinician recruitment will be conducted by the research coordinator or study staff, not by supervising physicians or direct clinical colleagues.

In addition to recruitment and enrollment, study procedures also involve iterative assessment of primary and secondary study outcomes (Table 1). Outcome assessment will be led by study staff and take place at scheduled in-person study visits or, if necessary, remotely over telephone or videoconferencing. These assessments will consist of a series of surveys and occur at baseline, 2, 4, and 6 months after randomization. Patient participants will be compensated $35 for completing each of the first three assessments (i.e., baseline, 2 month, 4 month) and $75 for completing the final 6-month close-out visit (total potential earnings $180). Purposive sampling will be used to recruit fifteen intervention participants who completed the final close-out visit to participate in a 45-minute semi-structured interview about their experience with IntACT. Compensation for completing the interview will be $75. If a participants misses study assessment visits, they will still be invited to conduct a study close-out visit at six months and complete the end of study survey.

Enrolled clinicians will complete an implementation survey after each exposure to IntACT (e.g., IntACT assists with discharge planning for a patient that they are caring for in the hospital). These surveys will use validated tools to assess the feasibility, acceptability, and appropriateness of IntACT, its specific components, and its implementation strategies from a clinician’s perspective. Purposive sampling will be used to recruit a subset of twelve clinicians who had extensive interactions with IntACT to complete semi-structured interviews further exploring experiences and perceptions related to the intervention. IntACT team members (n = 3) will be surveyed and interviewed one time at the end of the study period using these same assessment tools. IntACT team members will also complete a fidelity checklist one time for each new intervention patient enrollment documenting the clinical and psychosocial services provided. Clinician participants will be compensated $30 for completing each survey and an additional $75 for completing a 45-minute semi-structured interview.

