**Secondary Effectiveness Outcomes (compared between intervention and control groups)**				
Time to First Visit	Number of days elapsed between discharge and first primary care appt	EHR/admin	LR	Once/patient
Acute Care Utilization	# of ED, hospital, or urgent care visits during the 6 months preceding and 6 months following enrollment	PT	S, Qual	At 2, 4, and 6 months
Substance Use	Self-reported frequency and amount of substance use	PT	S, Qual	At 2, 4, and 6 months

**Abbreviations**: CT = clinical team (PCP, hospitalists, social workers). IT = IntACT team members. S = Survey. Qual = qualitative interviews or focus groups, Admin = administrative data. PT = patient. EHR = electronic health record. LR = logistic/linear regression

Primary effectiveness outcomes will be compared between intervention and control groups and include: 1) the percentage of participants who attend a follow-up visit (e.g., primary care, specialty care, SUD care) within 14 days of discharge, and 2) the percentage of participants with evidence of SUD care engagement at 2, 4, and 6 months following discharge, including attendance at scheduled visits and/or documentation of medication for substance use disorder receipt. Secondary effectiveness outcomes include: 1) time to first follow-up visit after hospital discharge; 2) self-reported substance use; and 3) acute care utilization including hospital readmission, ED visits, and urgent care visits. These outcomes will be assessed using a combination of administrative data review and patient self-report using the Timeline Followback method, an established framework for assessing recent substance use patterns [46,47].

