### Safety monitoring

This single-site, minimal-risk study does not require a formal Data and Safety Monitoring Board (DSMB). Study staff will monitor participants for adverse events potentially related to the intervention or research procedures, including confidentiality breaches and emotional or mental health distress during care coordination or data collection, as well as serious clinical outcomes (e.g., ED visits, hospitalizations, overdose, death) using the EHR and patient self-report during each study visit. Events that meet IRB reporting criteria will be reported according to institutional policy, and study procedures will be modified or paused if emerging safety concerns are identified.

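### Tables 1 and 2 do not match: patient-reported acute care before enrolment has no scheduled baseline collection, and substance use has no baseline on its follow-up instrument

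*Protocol article*

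**What the plan says.** Protocol article, Procedures and assessments, Table 1: the Timeline Followback row reads "TLFB (Substance Use and ED/Hospital Encounters; Follow-up visits only", with marks at months 2, 4 and 6 and none at baseline. The baseline column holds two substance-use items: "Baseline survey (demographics and substance use history questionnaire" and "TAPS (Baseline only". SF-12, PHQ-9 and GAD-7 are each marked at baseline and at all three follow-ups.

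Outcomes, Table 2, secondary effectiveness outcomes: acute care utilization is the number "of ED, hospital, or urgent care visits during the 6 months preceding and 6 months following enrollment". Its data source is PT (patient), its method is survey and qualitative, and its timing is "At 2, 4, and 6 months". Substance use is "Self-reported frequency and amount of substance use", with the same source and timing. The linkage, retention and time-to-first-visit rows list EHR/admin instead.

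Outcomes, text below Table 2: "These outcomes will be assessed using a combination of administrative data review and patient self-report using the Timeline Followback method". The sentence follows both the primary and the secondary list and does not say which source serves which outcome.

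Safety monitoring: staff follow "serious clinical outcomes (e.g., ED visits, hospitalizations, overdose, death) using the EHR and patient self-report during each study visit".

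**The concern.** The outcome definition asks for a 12-month window centred on enrolment, but the only patient instrument named for encounters starts at month 2. Two consequences follow if the tables are applied literally.

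First, pre-enrolment visits would have to be recalled months later. They would also be recalled after randomization, by participants who know their arm. A baseline answer would avoid that, because the baseline survey is completed before randomization. With the patient as sole source and complete-case analysis as the primary approach, a participant who misses visits may also drop out of the acute-care count.

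Second, substance use is the one repeated patient-reported measure in Table 1 without a baseline value on its own instrument. Follow-up use cannot be expressed as change or adjusted for the same quantity at entry. With 45 and 30 participants per arm, chance differences in prior use are likely enough to matter when the estimates are read.

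The article says the broad outcome set is there to test the assessment approach for a later trial, so a schedule that does not fit its own outcome definition bears on the pilot's purpose.

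**Working it through.** The plan gives no figure for this point and no power calculation, so there is nothing to reproduce. The check has two parts.

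**1. Schedule against definition**

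- Window required (Table 2): 6 + 6 = 12 months.
- TLFB visits (Table 1): months 2, 4 and 6. Baseline: 0.
- Look-back needed to reach 6 months before enrolment: 2 + 6 = 8 months at month 2, 4 + 6 = 10 at month 4, and 6 + 6 = 12 at month 6. The 12-month case can occur, because participants who miss earlier assessments are still invited to the six-month close-out.
- No recall period is stated. If each TLFB covers only the time since the previous visit (an assumption), the three visits cover 2 + 2 + 2 = 6 of the 12 months and none of the pre-enrolment half.
- Baseline substance-use instruments: two (TAPS and the history questionnaire). Neither is repeated, and neither is the TLFB.

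**2. What a same-scale baseline could buy (illustration)**

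Inputs: 75 patients (Recruitment and eligibility) and 3:2 allocation (Study design), so 75 × 3/5 = 45 and 75 × 2/5 = 30. Assumed, not in the document: two-sided alpha 0.05, power 80%, and baseline-to-follow-up correlation r = 0.3, 0.5 or 0.7.

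- Standard error of a standardized difference: √(1/45 + 1/30) = 0.236. A chance baseline difference above 0.25 SD in either direction corresponds to |z| > 0.25/0.236 = 1.06, a probability of about 29%.
- Detectable standardized difference without a baseline covariate: (1.960 + 0.842) × 0.236 = 0.66.
- With the covariate, residual variance is multiplied by 1 − r², the detectable difference by √(1 − r²), and the equivalent sample size is 75/(1 − r²):

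| r | 1 − r² | Detectable difference | Equivalent n |
|---|---|---|---|
| 0.3 | 0.91 | 0.63 | 82 |
| 0.5 | 0.75 | 0.57 | 100 |
| 0.7 | 0.51 | 0.47 | 147 |

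This table compares with no adjustment at all. If TAPS or history were used instead and correlated with follow-up use at some r′, the relevant ratio is (1 − r²)/(1 − r′²). For example, with r = 0.5 and r′ = 0.3 it is 0.75/0.91 = 0.82 rather than 0.75, and with r = 0.7 and r′ = 0.5 it is 0.51/0.75 = 0.68 rather than 0.51. The r′ values are also assumed.

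**The case against.** The best defence is that the Outcomes text already names administrative data review. Pre-enrolment visits can be taken from records at any time, so a reader who infers that acute care utilization cannot be produced, or that its pre-period is lost for good, goes further than the document. Nor does the document show that patients are never asked: no TLFB recall period is given, and the items of the baseline questionnaire are not shown. This stands. What remains is that Table 2 lists the patient alone for this row. The general sentence about combined sources can also be read as records for the primary outcomes and TLFB for these two. Records may miss visits outside the system.

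A reader might also infer that substance use has no baseline at all. Table 1 contradicts that: TAPS and the history questionnaire are both taken at baseline. A covariate need not share the outcome's scale, and the covariate set is commonly left to the analysis plan.

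Three further inferences are not supported:

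- **Urgent care is not collected.** The TLFB row label omits it, but a row label is not an item list, and the text includes urgent care.
- **The index admission is counted in both windows.** The text speaks of readmission for follow-up, and the counting rule belongs to the analysis plan.
- **Visit counts are given the wrong model.** Regression is to be used as appropriate, and Table 2 does not assign it to this row.

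Finally, the trial has no power target to lose, declares no change-from-baseline analysis, and takes both primary effectiveness outcomes from EHR/admin data.

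**Conclusion.** The point holds as a mismatch between two tables. Table 2 assigns a pre-enrolment window to patient report, Table 1 schedules no collection aimed at it, and the text that could resolve this does not say which source covers which window. By patient report alone, the look-back is 8 to 12 months. Separately, substance use has baseline information but none on the TLFB scale.

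Severity is moderate. These are secondary outcomes in a pilot that is not powered for effectiveness, and the comparison between randomized arms is valid without the change. The precision gain rests entirely on assumed correlations: residual variance of 0.91 to 0.51 against no adjustment for r from 0.3 to 0.7, and a smaller gain if TAPS or history is already used.

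**What to change.** - **Table 2, acute care utilization:** change the source from PT to EHR/admin plus self-report, for both the pre- and post-enrolment windows.
- **Table 1, TLFB row:** add a baseline mark, covering substance use before admission and ED, hospital and urgent care visits in the previous 6 months. Name urgent care in the row label and state the recall period for each visit.
- **Analysis:** use the baseline value as a covariate for the TLFB outcomes.

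The cost is an edit to two tables and a somewhat longer baseline interview for hospitalized patients. Staff already review the EHR for ED visits and hospitalizations under Safety monitoring, so part of the record work exists. Pre-enrolment encounters can be added from records later, but a baseline TLFB taken before randomization cannot, so that change should be made before recruitment opens (scheduled for June 21, 2026).

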### Outcomes

The outcomes of the IntACT trial are represented in Table 2. Primary implementation outcomes include feasibility, acceptability, appropriateness, reach, and cost. Clinician participants and IntACT team members will complete validated survey instruments and semi-structured interviews evaluating the feasibility, acceptability, and appropriateness of the IntACT intervention. These assessments will assess the implementation of IntACT overall, along with its specific intervention components and implementation strategies from the IRLM (Fig 2). Reach will be assessed using administrative data (e.g., EHR, study records) denoting the number of clinicians and community follow-up sites that interact with IntACT. Costs will consist of estimated intervention costs (e.g., team member salary and effort, cell phone).

**Table 2 pone.0359281.t002:** IntACT pilot study key outcomes.

Pilot Trial Measures				
Variable	Measure	Data Source	Method	Frequency
**Implementation Outcomes**				
Acceptability	4-item Acceptability of Intervention Measure, Interviews	CT, IT, PT	S, Qual	End of Exposure
Appropriateness	4-item Intervention Appropriateness Measure, Interviews	CT, IT, PT	S, Qual	End of Exposure
Feasibility	4-item Feasibility of Intervention Measure, Study Enrollment	CT, IT, PT	S, Qual	End of Exposure
Reach	Number of Pt and PCP who participate in and complete the study	EHR/admin	S, Qual	Monthly
Cost	Costs of intervention staffing, training, and infrastructure	Admin	Admin	Quarterly
**Primary Effectiveness Outcomes (compared between intervention and control groups)**				
Care Linkage	% of participants attending an outpatient visit within 14 days of discharge	EHR/admin	LR	Once/patient
Treatment Retention	% of patients with evidence of SUD treatment engagement (e.g., active prescription, visit with associated SUD diagnosis within past month)	EHR/admin	LR	At 2, 4, and 6 months
